### **2. Study setting and recruitment**

The study will commence on September 1, 2018, and will be completed by December 31, 2020, at the Guang'anmen Hospital, China Academy of Chinese Medical Sciences and the South Area of Guang'anmen Hospital, China Academy of Chinese Medical Sciences. DED is diagnosed according to the criteria of International DEWS by an experienced ophthalmologist. The participants identified as eligible will be randomized into two groups—acupuncture and medicine—at a ratio of 1:1. The flowchart of the trial is shown in Figure 1. The total study period for this trial is 32 weeks (Figure 2), including 8-week treatment period and 24-week follow-up period.

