#### **5. Randomization and blinding**

The randomization will be performed by the Drug Clinical Trial Office affiliated with Guang'anmen Hospital using a centralized computer system. Patients were randomly assigned to the acupuncture or AT group using a block size of 4 stratified by centers, the final group assignments were placed in 120 opaque sealed envelopes, which were serially numbered and kept by a researcher not involved in treatment procedures or data analysis. After informed consent was obtained, the researcher opened the envelope according to the order in which the participant entered the trial and was provided for the prescribed treatment. All participants received either acupuncture or ATs 3 times per week over the 8-week period, and both groups were followed up for another 24 weeks.

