#### **6. Data collection**

The data collection will be from the case report forms recorded by the investigator in the trial. The demographic, clinical, and examination results of DED from the

participants will be recorded at baseline and during the treatment and follow-up periods. Moderate to severe DED will be diagnosed by an experienced ophthalmologist after an ophthalmology examination. The investigator will enter all of the collected data into the case report forms. During the treatment period (8th week) and the follow-up period (32nd week), the forms concerning the questionnaire survey will be completed by the participants under the guidance of a full-time staff member; other forms concerning the ophthalmology examination will be filled in by the investigator according to objective examination results.

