## **9. Statistical analysis**

SPSS Version 26.0 (International Business Machines Corporation, China) software will be used to perform the statistical analysis. Two-sided tests will be used for all statistical analyses. The level of significance is established at 0.05. Efficiency and safety analyses will be based on all participants at randomization according to the intention-to-treat (ITT) principle. All participants who have accepted randomization will be included in the statistical analysis of data. All original data collected from participants in the trial will be included in the full statistical analysis set. The data cannot be changed or eliminated at random. The missing data in the case report forms will be replaced by using the last observation carried forward method.We will do sensitivity analyses in the per protocol set, which included all randomised patients who had no major protocol deviation.

We will use the mean and standard deviation (SD) to describe continuous data if the data have a normal distribution and the mean and 95% confidence interval (CI) to describe continuous data if the data are skewed. We will use the percentage or 95% CI to describe categorical data. For comparisons with baseline data, we will use a paired *t*-test for continuous data and a nonparametric test for categorical data. For comparisons of the differences between the two groups, T-tests or Mann–Whitney U tests will be used for comparisons between continuous variables, and chi-square tests or Fisher's exact tests will be used for comparisons between categorical variables, as appropriate.

For assessing safety in the trial, the investigator will present the AEs and adverse reactions with tables, which will comprise the categories of AEs, the severity of AEs, the incidence of AEs, and correlation with the treatment. Every participant with serious AEs will stop receiving the intervention. All details will be reported in a timely manner.

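### Groups are compared without baseline adjustment although SIT, NRS, OSDI, TBUT and CFS are all measured at week 0, so the unbiased comparison gives up precision

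*Combined protocol and SAP*

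**What the plan says.** - **Between-group test.** Section 9 (Statistical analysis) speaks of comparing differences between the arms and states: "T-tests or Mann–Whitney U tests will be used for comparisons between continuous variables". Chi-square or Fisher tests follow for categorical variables, and the choice among all of these is left to whichever is appropriate. No ANCOVA, regression, mixed model or covariate is named.
- **Use of baseline.** In the planned tests, baseline appears only in this sentence: "For comparisons with baseline data, we will use a paired *t*-test for continuous data". That describes change from baseline and does not estimate a difference between arms.
- **Data available.** Section 6 (Data collection) says that results from "participants will be recorded at baseline and during the treatment and follow-up periods". The schedule in Figure 2 marks SIT, NRS, OSDI, TBUT and CFS at weeks 0, 4, 8 and 32. Acceptance is marked at week 8 only.
- **Size and error rate.** The only indication of sample size is in section 5: "the final group assignments were placed in 120 opaque sealed envelopes". Section 2 gives two arms, "acupuncture and medicine—at a ratio of 1:1". Section 9 adds "Two-sided tests will be used for all statistical analyses" and "The level of significance is established at 0.05". No power, effect size, SD, dropout rate or correlation is given.
- **Stratification.** Section 5 stratifies randomization by center. Section 9 does not use center.

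**The concern.** For five outcomes the most useful covariate, the same measure at week 0, is already collected but is left out of the comparison that estimates the treatment effect. With about 60 per arm, chance differences at baseline add noise to a comparison of final values and, with the opposite sign, to a comparison of changes. Adjustment removes most of that noise. With a common slope and one degree of freedom spent, it is in expectation never less efficient than either unadjusted t-test.

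Two further points are left open. The word for what is compared in section 9 can mean a difference between arms in the final values, or changes from baseline compared between arms. There is also no rule for choosing between the t-test and Mann–Whitney, which target different quantities; Mann–Whitney gives no mean difference. Two scales and two tests make four possible analyses per outcome and visit. A prespecified baseline-adjusted model closes both choices, because its treatment estimate is the same whether the response is the final value or the change.

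**Working it through.** **The plan's own figure.** The 120 cannot be reproduced, because no design inputs are given. As a back-calculation only (normal approximation), 60 per arm gives 80% power for a standardized difference of (1.960 + 0.842) × √(2/60) = 0.51.

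**Inputs from the documents.** N = 120 (envelopes, section 5); 1:1, so 60 per arm (section 2); two-sided 0.05 (section 9).

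**Assumptions, not in the documents.** All 120 are analysed; baseline-outcome correlation r = 0.3, 0.5 or 0.7; equal SDs at baseline and follow-up; for power, a true difference of 0.5 SD.

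**Step 1: relative variance of the treatment effect.** Final values: 1. Change scores: 2(1 − r). ANCOVA: 1 − r².

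**Step 2: number an unadjusted t-test would need to match ANCOVA on 120.**
- Against final values: 120/(1 − r²).
- Against changes: 120 × 2(1 − r)/(1 − r²) = 240/(1 + r).

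| r | ANCOVA variance | Change variance | N to match, final values (extra) | N to match, changes (extra) |
|---|---|---|---|---|
| 0.3 | 0.91 | 1.40 | 131.9 (11.9) | 184.6 (64.6) |
| 0.5 | 0.75 | 1.00 | 160.0 (40.0) | 160.0 (40.0) |
| 0.7 | 0.51 | 0.60 | 235.3 (115.3) | 141.2 (21.2) |

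The two columns run in opposite directions with r. Charging ANCOVA for its one degree of freedom (factor 118/117) changes the final-value gains only to 10.8, 38.6 and 113.3.

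**Step 3: power, 60 per arm, 0.5 SD.** Two-sample t-test power at a standardized difference of 0.5/√(relative variance):

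| r | Final values | Changes | ANCOVA |
|---|---|---|---|
| 0.3 | 77.5% | 63.1% | 81.3% |
| 0.5 | 77.5% | 77.5% | 88.0% |
| 0.7 | 77.5% | 93.9% | 96.7% |

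**Step 4: lower correlation.** At r = 0.2 the gain over final values is 120/0.96 − 120 = 5.0, and over changes 240/1.2 − 120 = 80.0.

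**Step 5: unequal SDs.** Section 3 restricts entry (SIT below 10 mm in 5 minutes, TBUT below 10 seconds, a symptom NRS of at least 4, CFS of at least 1). This can shrink the baseline SD and lower r. With baseline SD = k × follow-up SD, the change-score variance is 1 + k² − 2rk, and the N to match is 120(1 + k² − 2rk)/(1 − r²):

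| k (illustrative) | r = 0.3 | r = 0.5 | r = 0.7 |
|---|---|---|---|
| 1.0 | 184.6 | 160.0 | 141.2 |
| 0.7 | 141.1 | 126.4 | 120.0 |
| 0.5 | 125.3 | 120.0 | 129.4 |

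With k at 0.5 or 0.7 the gain over changes is therefore about 0 to 21 participants. The final-value column of Step 2 depends on r but not on k.

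**The case against.** The strongest case against the point is that the planned analysis is legitimate and the size of the gain is unknown.

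- **Validity.** A reader might infer that omitting baseline biases the result. The documents do not support that. Allocation is randomized, so the unadjusted comparison is unbiased and keeps its type I error; chance imbalance is already reflected in the standard error. This objection stands, and the loss is one of precision.
- **Magnitude.** Correlation, SD ratio, effect size and number analysed are all assumed. A low correlation makes the gain over final values trivial (5 participants at r = 0.2), and a smaller baseline SD can make the gain over changes vanish. This stands too. It limits confidence in any single figure but leaves the direction of the argument unchanged: a low r that makes adjustment nearly worthless against final values makes it worth most against changes when the SDs are equal, and the plan leaves both comparisons open.
- **Scope.** A reader might infer that every outcome could be adjusted. Figure 2 shows Acceptance at week 8 only, and adverse events have no baseline score. The point is confined to the five measures taken at week 0.
- **Data-driven choice of test.** A reader might infer that the sponsor means to pick the test after seeing results. Section 9 does not say so, and the same paragraph separates normal from skewed data when describing summaries. What can fairly be said is that no selection rule is given.
- **Scale.** The formulas apply to t-tests of continuous outcomes. They are approximate for Mann–Whitney and for graded CFS, which the plan may treat as categorical.

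**Conclusion.** The point holds as a matter of efficiency and prespecification. Section 9 leaves out of the between-group comparison a baseline value that is collected for SIT, NRS, OSDI, TBUT and CFS, and it does not settle whether final values or changes are compared.

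Under the stated assumptions (120 analysed, equal SDs, r from 0.3 to 0.7), ANCOVA is worth about 12 to 115 extra participants against a t-test of final values and about 21 to 65 against a t-test of changes. At r = 0.5 both figures are 40, and power for an assumed 0.5 SD difference goes from 78% to 88%. These ranges illustrate the possible gain; they are not estimates for this trial. The plan should make this change, but leaving it as it is would not invalidate the trial's result.

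**What to change.** In section 9:

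1. For SIT, NRS, OSDI and TBUT, make the main between-group analysis an ANCOVA at a visit named in advance, with the week 0 value and center as covariates. A mixed model over weeks 4, 8 and 32 with the same two terms is an alternative. The plan at present designates no primary visit and contains no repeated-measures model, so whichever is chosen has to be specified from the start.
2. Report the adjusted mean difference with its 95% CI. This also removes the ambiguity between final values and changes.
3. Analyse CFS with a model suited to its graded scale (for example, a proportional-odds model), also including its week 0 value and center.
4. Keep a rank-based test only as a sensitivity analysis for skewed outcomes.
5. Leave Acceptance and adverse events as unadjusted comparisons, since they have no week 0 value.

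The cost is SAP wording, a decision on the visit, and slightly more analysis work. No extra visits, participants or measurements are needed.

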| NRS                |              | ×          | ×               | × | ×  |
| OSDI               |              | ×          | ×               | × | ×  |
| TBUT               |              | ×          | ×               | × | ×  |
| CFS                |              | ×          | ×               | × | ×  |
| Acceptance         |              |            |                 | × |    |

Figure. 2 Standard protocol items: recommendation for interventional trials (SPIRIT) schedule of enrolment, interventions, and assessments. SIT, Schirmer-I test; VAS, visual analogue score; OSDI, ocular surface disease index ; TBUT, tear film breakup time; CFS, corneal fluorescein staining.
